## Abstract

**Background:**

Overweight and obesity are major health problems worldwide. This protocol describes the HEALTHI (Healthy Eating and Active LifesTyle Health Intervention) Program, a 12-week randomised-controlled weight-loss intervention that adopts two theory-based intervention techniques, *mental imagery* and *implementation intentions*, a behaviour-change technique based on planning that have been shown to be effective in promoting health-behaviour change in previous research. The effectiveness of goal-reminder text messages to augment intervention effects will also be tested. The trial will determine the effects of a brief, low cost, theory-based weight-loss intervention to improve dietary intake and physical activity behaviour and facilitate weight-loss in overweight and obese individuals.

**Methods/Design:**

Overweight or obese participants will be randomly allocated to one of three conditions: (1) a psycho-education plus an implementation intentions and mental imagery condition; (2) a psycho-education plus an implementation intentions and mental imagery condition with text messages; or (3) a psycho-education control condition. The intervention will be delivered via video presentation to increase the intervention’s applicability in multiple contexts and keep costs low. We hypothesise that the intervention conditions will lead to statistically-significant changes in the primary and secondary outcome variables measured at 6 and 12 weeks post-intervention relative to the psycho-education control condition after controlling for baseline values. The primary outcome variable will be body weight and secondary outcome variables will be biomedical (body mass, body fat percentage, muscle mass, waist-hip circumference ratio, systolic and diastolic blood pressure, low-density lipoprotein, high-density lipoprotein, total cholesterol, triglycerides, blood glucose and insulin levels), psychological (quality of life, motivation, risk perception, outcome expectancy, intention, action self-efficacy, maintenance self-efficacy, goal setting and planning), and behavioural (self-reported diet intake, and physical activity involvement) measures. We also expect the intervention condition augmented with text messages to lead to statistically significant differences in the primary and secondary outcome variables at the follow up periods after controlling for baseline values.

**Discussion:**

The planned trial will test the effectiveness of the theory-based HEALTHI program intervention to reduce weight and salient psychological, biomedical, and behavioural outcomes in overweight and obese adults. The study has been designed to maximise applicability to real world settings and could be integrated into existing weight management practices.

**Trial registration:**

ACTRN: ACTRN12613001274763. Registration date 19/11/2013.

## Background

### The problem of overweight and obesity

Obesity and overweight are linked to major chronic illnesses and conditions like cardiovascular disease, diabetes, and certain cancers [1]. It is recognised as a global problem with obesity rates worldwide having nearly doubled since 1980 [1]. This has led researchers to develop effective means to assist obese and overweight individuals to reduce their weight and, in doing so, their risk of chronic illness. The main cause of weight gain is an imbalance between the amount of energy consumed and expended by individuals. Wing and Hill [2] report that weight-loss can only be achieved through a negative energy balance, decreasing energy intake by restricting food or increasing energy expenditure through daily activity. Based on current evidence, weight-loss strategies that include a combination of a reduced calorie intake diet and increased physical activity appear to be most effective [3,4]. The current article will discuss the development of a brief, cost effective, theory-based intervention using implementation intentions and mental imagery techniques to target dietary intake and physical activity behaviour to promote weight-loss. The intervention will involve minimal direct contact between participants and practitioner and will use resources that can easily be ‘rolled-out’ in ‘real world’ contexts. The intervention will use the Health Action Process Approach (HAPA) [5] as a theoretical basis for intervention content and to explain the mechanisms behind the proposed effects. The intervention will also incorporate the use of goal reminder text messaging to augment the intervention effectiveness.

### Diet, physical activity, and weight loss

Research suggests that combining a calorie-reduced diet and regular physical activity will be effective in achieving weight loss and preventing obesity related risk factors [3,6-9]. Reducing 500 calories per day can assist with a weight-loss of approximately 0.5 kilograms a week [10,11]. Fernau [10], suggests that one strategy that individuals may use to manage the consumption of food is to count daily calories. Some of the methods to assist with calorie counting are to spread calories throughout the day, read labels including the serving size and calories per serving, use a calorie counter such as a book or website, and monitor daily food and drink intake such as through the use of a food diary (*see* Fernau 2010, for more information) [10].

Engaging in regular physical activity is also an important part of an effective strategy to assist an individual to expend more calories than the body requires thereby contributing to weight loss. Exercise can assist in improving risk factors associated with cardiovascular disease even in the absence of weight-loss [7,9,12,13]. Physical activity guidelines in America and Australia recommend that adults engage in a minimum of 30 minutes of moderate activity on most or all days of the week to receive health benefits [14]. A combination of changes in dietary intake and physical activity behaviour will likely be most effective in assisting an individual to lose weight [3,4].

### Changing health behaviour

For health professionals to support clients to lose weight, it is necessary to identify the factors related to health-related behaviour change and use them as a basis for intervention design [15,16]. These factors are outlined in many different behaviour change models, particularly social psychological models which aim to explain intentional and motivated behaviour that have been applied to predict and understand health behaviour [17]. Researchers seeking behavioural solutions to health-behaviour need to target psychological factors that are considered changeable and malleable to evoke health-behaviour change. These psychological factors can be targeted by sets of behaviour-change techniques that can evoke a change in the psychological factors linked to health behaviours [18,19].

The current intervention adopts the HAPA [5], an integrated social psychological model that has been widely used to identify the components related to changes in weight loss behaviours and how components can be used to inform the intervention content to ensure the change process is clearly identified (see Figure 1). The HAPA states that the process of health behaviour change consists of two phases: a motivational phase that leads an individual to form the intention to change their behaviour, and a volitional phase that leads the individual to performing the actual behaviour [5]. Two strategies that map closely on to the volitional and motivational phases of the HAPA include implementation intentions and mental imagery, respectively. The intervention components are designed to target both the motivational and implemental phases of the HAPA. The components are proposed to lead to optimal behaviour change by providing individuals with the confidence and motivation to engage in the behaviour, as well as the capacity to convert motivation into actual behaviour change [20].

**Figure 1 Fig1:**
[figure not shown]
**Health action process approach model (Schwarzer, 2008).**

Mental imagery has been found to increase an individual’s confidence in their ability to change their behaviour (self-efficacy), which relates to the motivational phase in the HAPA. Mental imagery can be categorised as either being outcome imagery or process imagery, both which have different implications for goal attainment [21-23]. Outcome imagery is based on imagery related to the experience of goal achievement and success, and therefore is a motivational approach for improving goal achievement. Process imagery is based on imagery related to the steps needed to achieve the desired outcome, which according to Pham and Taylor [24] is mainly a cognitive planning strategy [23]. Implementation intentions are action plans that state when, where, and how an individual intends to reach a goal and promotes action planning, bridging the gap between having the intention to change behaviour and performing the behaviour, consistent with the volitional phase of the HAPA [20,25]. To target changes in diet and physical activity behaviours for weight-loss, the combined use of implementation intentions and mental imagery have been found to be an effective method [26].

Mobile phone text messaging is a widely available, cost effective, and an instant tool that has been recently applied to promote health behaviour change and to increase intervention effectiveness [27]. Support for the use of text messages to increase intervention effectiveness is found within various studies exploring the outcome of weight-loss [28-31]. For example, Prestwich and colleagues [31] developed an intervention aimed in promoting brisk walking among sedentary individuals. The researchers found that pairing implementation intentions with goal reminder text messages assisted participants in increasing walking frequency and weight loss. Text messages which include goal reminders may enhance the effectiveness of both implementation intentions and mental imagery steps, respectively within the volitional and motivational phase of the HAPA; The use of text message goal reminders can serve to “boost” the effectiveness of these intervention components as that may assist participants in recalling their goals and plans increasing their commitment to action them, as well as increasing ones confidence to change their behaviour.

## The present study

The purpose of the current study is to develop and evaluate the HEALTHI (Healthy Eating and Active LifesTyle Health Intervention) program, a theory-based intervention to change dietary intake and physical activity behaviours, and promote weight-loss and the reduction of obesity-related health risk factors in a sample of overweight and obese individuals. The key behavioural outcome will be changes in body weight through engagement in, and adherence to, a calorie-restricted diet and participation in 30 minutes of daily physical activity. Although a number of studies have incorporated the use of implementation intentions and mental imagery to promote health behaviour [21-23,32] the present intervention will incorporate the use of both strategies to promote both diet and physical activity guidelines adherence. The inclusion of both strategies acting synergistically with multiple longer-term follow-up of biomedical, behavioural, and psychological outcomes is a unique aspect of the current intervention and will contribute to knowledge by demonstrating whether these techniques are effective in bringing about weight loss and other outcomes changes.

The present intervention will also incorporate the use of technology, augmenting the effectiveness of the intervention with goal-reminder text messages delivered by mobile phone. The use of multiple strategies in achieving weight loss goals including implementation intentions, mental imagery and text message goal reminders is a unique aspect of the current study. Pairing implementation intentions with text message goal reminders has been shown to be successful for weight-loss and participation in physical activity [31]; the aim of the study is to not only deliver implementation intention, but also mental imagery goal reminder text messages based on the HAPA. This is important as research has shown that only a few studies using text messaging for behaviour change in disease prevention and treatment had a theoretical rationale to guide various interventions [27]. This will be the first study to demonstrate the use of both text messaging with implementation intention and mental imagery in weight management. This will address a specific gap in the research literature regarding weight management and will contribute to knowledge by testing the proposal that introducing multiple theory-based behaviour-change strategies alongside a standard weight-change intervention program will improve the effectiveness of the intervention [33,34].

### Hypotheses

The main hypothesis is that the intervention conditions adopting implementation intentions and mental imagery techniques, will result in statistically-significant independent improvements in the outcome measures relative to the control condition from the time of intervention and at 6 and 12 weeks. We also expect statistically-significant differences in the outcome variables across the two intervention conditions, such that the intervention condition with text messages leads to greater weight loss that the intervention condition alone.

It is also hypothesised that relative to baseline and week 6 and 12, the intervention with text message condition will lead to statistically-significant independent improvements on the biomedical, psychological, and behavioural outcome measures, compared with the intervention and control conditions. In particular, we expect to find statistically-significant differences in the key HAPA-based psychological mediators of the effects of the intervention components including planning (relevant to implementation intentions) and self-efficacy and motivation (relevant to mental imagery) over the same follow-up time points.

## Methods and design

### Design

A randomised controlled design will include obese and overweight participants randomly allocated to one of three conditions: A psycho-education control condition (control condition), an implementation intention and mental imagery techniques condition (intervention condition), and an implementation intention and mental imagery techniques with text messages condition (intervention with text message condition). Figure 2 displays the design of the intervention and proposed participant flow through the study. The 12-week study will examine the effects of the intervention on biomedical, psychological, and behavioural outcome measures at baseline and post intervention (at 6 and 12 week follow-ups). The study information and intervention manipulations will be delivered via a video presentation viewed at baseline. See Table 1. While viewing the video intervention manipulations participants will be asked to complete various activities such a goal setting. The responses to the intervention activities will be emailed to the research team to indicate program compliance and adherence. Ethical approval for the trial has been obtained from Curtin University’s Human Research Ethics (approval number: HR137/2013). The trial has been registered on ANZCTR (Trial number: ACTRN12613001274763).

**Figure 2 Fig2:**
[figure not shown]
**Participant flow diagram.**

**Table 1 Tab1:** **Study components specific to each condition**

**Conditions**		
***Control***	***Intervention***	***Intervention with text message***
● Study information	● Study information	● Study information
● Psycho-education	● Psycho-education	● Psycho-education
● Weight loss guidelines	● Weight loss guidelines	● Weight loss guidelines
● Goal setting	● Goal setting	● Goal setting
	● Implementation intentions	● Implementation intentions
	● Mental imagery	● Mental imagery
		● Text messages

### Participants

Participants will be recruited via the Curtin University website and email system, flyers in local community organisations, a Western Australian Newspaper and a social-networking website. Eligible respondents recruited via these procedures will be provided with study information and an online link to a corresponding online questionnaire (Qualtrics™). Participants will be directed to complete the online screening questionnaire to ensure they meet the study inclusion criteria. Participants are eligible for inclusion if they are aged between 18 and 65 years, overweight or obese, defined as a body mass index (BMI) of between 25 and 40, and cite a willingness to have blood samples and body composition scans taken. Study exclusion criteria include serious health conditions, inability to engage in any form of physical activity, pregnancy, severe depression, inability to commit to follow up clinic sessions, or no access to a mobile phone with text message features. A comprehensive list of the inclusion and exclusion criteria is provided in Appendix A.

Participants that meet the study inclusion criteria will be invited to attend an initial orientation session at the Curtin University clinic to provide them with study information. Individuals are then given an opportunity to officially enrol in the program at the orientation session. Prior to their first clinic appointment the participants will be directed to complete baseline measurements.

## Intervention protocol

### Procedure

The study will adopt a double-blind procedure so that both the participant and researcher are unaware of the intervention conditions to which they have been assigned. A research assistant naïve to the purpose of the study will ensure each participant is provided with a participant identification number and randomly allocated to one of the three conditions using a computer-generated schedule [35].The intervention information and procedures for each of the three conditions will be determined by the allocated condition and participants will be required to access the video presentation corresponding to their allocated condition. Participants in the intervention with text message condition, will have their participant identification number matched to their mobile phone number. The mobile numbers will be entered on a text message system to allow the researcher to send participants their weekly text message goal reminders.

Participants will need to provide written consent prior to participation. Prior to each clinic appointment participants will complete questionnaires measuring baseline psychological and behavioural outcomes including a 3 day food, drink, and exercise diary. Within a three day period, prior to their clinic appointment, participants will be required to attend to a pathology clinic to take blood sample measures. Furthermore, at each clinic appointment participants will engage in baseline biomedical assessments: blood pressure, weight, waist-hip ratio, and at baseline and week 12 body composition measures. At the first clinic appointment participants will be asked to view a pre-recorded video presentation that contains the intervention information, followed by the completion of a questionnaire containing the post-intervention measures. One of two video presentations will be provided to participants, one designed for the control condition participants, and the other for the two intervention conditions. The duration of the video presentation is approximately 60 and 76 minutes for the control and intervention conditions respectively. Due to the pauses in the video to complete various activities and the break time the intervention manipulation duration may last approximately 90 to 120 for the control condition, and 150 to 210 for the intervention conditions. In addition, participants allocated to the intervention with text message condition will receive goal reminder text messages over the 12 weeks of the intervention. Prior to leaving the clinic, all participants will be provided with their future appointment times and a set of tools to assist them with monitoring their physical activity and calorie intake: A copy of the Calorie King™ book [36], Calorie Counter diary [37], the Australian dietary guidelines [38], and Australian physical activity guidelines [39]. Participants will be encouraged to contact the researcher if any queries arise. In addition, a personalised email providing a handout of the essential program information such as the guidelines and the participant’s responses to various activities (including goals) when watching the video presentation will be sent to the participant via email. The participant responses to the activities will be assessed by the research team to ensure program compliance.

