Delivery mode = intervention delivered via online Qualtrics™ with incorporated video presentation.

One condition will receive goal reminder text messages.

Intensity time = participants are asked to view the intervention once and complete the various activities incorporated within the intervention.

Setting = Clinic room within Curtin University.

For example, the objective *“*monitor your energy intake to ensure your calorie (or kilojoule) intake is somewhere in-between the minimum and maximum allowance amount” is listed as the behavioural objective or behaviour needed to be changed (Table 2). The intervention components are based on theory-based psychological concepts: risk perception and planning. The planning variable target is matched with the behaviour change techniques of implementation intentions. The implementation intentions relate to the use of the strategy of directing participants to create if-then plans in relation to the diet guideline. The strategy will be evaluated by having participant’s complete self-reported questionnaires on planning and the if-then plan will be evaluated by the researcher.

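### The claim that the researcher is blind to condition conflicts with the researcher's own tasks, and no blinded assessor or coder is named, so blind measurement is not assured

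*Protocol article*

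**What the plan says.** The blinding claim is in the protocol article, Intervention protocol, Procedure: "The study will adopt a double-blind procedure so that both the participant and researcher are unaware of the intervention conditions". Allocation is given to someone else: "A research assistant naïve to the purpose of the study will ensure each participant is provided with a participant identification number and randomly allocated".

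The same paragraph then describes the text-message arm. "Participants in the intervention with text message condition, will have their participant identification number matched to their mobile phone number", and the numbers go onto a messaging system "to allow the researcher to send participants their weekly text message goal reminders". The notes under Table 2 confirm that "One condition will receive goal reminder text messages".

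On written responses, the discussion of Table 2 says that "the if-then plan will be evaluated by the researcher". The Procedure section adds: "The participant responses to the activities will be assessed by the research team to ensure program compliance". Table 1 lists implementation intentions and mental imagery for the two intervention conditions only, and goal setting for all three.

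The Biomedical outcomes section describes the instruments but not who operates them. The Psychological measures section says that goals, plans and imagery steps are coded on whether they are suitable and realistic, and names no coder.

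**The concern.** Blinding is a stated protection, and readers will rely on it. Under Weight-loss information for all participants, the article argues that differences between arms can be put down to the intervention components alone. That argument is weaker if someone who knows the arm also measures, codes or advises participants.

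The article gives the researcher two tasks that reveal condition, and participants are also invited to bring queries to the researcher. If that person also takes waist and hip circumference by tape, or judges the free-text goals, expectation could enter those outcomes. Goal setting is listed in the abstract as a secondary outcome, so its coding is not only a process check.

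**Working it through.** There is no figure to reproduce, because the point depends on no sample size, power or alpha. The check sets the blinding claim beside each task and asks what that task reveals.

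| Task | Who does it, as written | Arms concerned | What it reveals |
|---|---|---|---|
| Allocation | Research assistant | All | Condition, but this is a separate role from the researcher |
| Matching ID to phone number | Not stated | Text arm only | Text arm |
| Weekly texts for 12 weeks | The researcher | Text arm only | Text arm |
| Evaluating if-then plans | The researcher | Two intervention arms | Intervention versus control |
| Assessing activity responses for compliance | The research team | All; plans and imagery in two arms only | Intervention versus control, for whoever reads them |
| Clinic measurements | Not stated | All | Depends on who does it |
| Coding goals | Not stated | All | Nothing, if kept apart from plans and imagery |

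**Step 1: is researcher blinding contradicted?** Yes. The article separates the allocating assistant from the researcher, so the researcher's tasks cannot be read as the assistant's. Sending messages to one arm for 12 weeks, and evaluating plans that controls do not write, are both incompatible with being unaware of condition. No other section resolves this.

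**Step 2: how many participants?** The article plans to recruit 102 and gives no allocation ratio. Assuming equal arms, 102/3 = 34 are in the text arm and 2 × 34 = 68 are in the two intervention arms. Texting bears on about 34. The plans mark about 68 as not control, but they do not separate the two intervention arms, which watch the same video.

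**Step 3: when does the information arise?** The plans are written while viewing the video at baseline, and the Design section has activity responses emailed to the research team. The information can therefore be available before the 6- and 12-week measurements.

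**Step 4: does it reach outcome measurement?** This cannot be settled. It does so only if the person who texts or reads plans also measures, or if measurers can see that information. The article is silent on both. There is one further route: the clinic session is put at about 90 to 120 for control and 150 to 210 for the intervention conditions (no unit is printed; minutes assumed). The ranges do not overlap, so staff present at the baseline session could infer intervention versus control.

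**Step 5: which outcomes would be exposed?** Waist and hip are taken by tape, twice and averaged, and depend most on the operator. Goal coding is a judgement. Weight (the primary outcome) comes from a digital scale, blood pressure from an automated monitor with three readings averaged, body composition from DEXA, and blood values from a pathology laboratory. These are less exposed.

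**The case against.** A reader might infer that outcome measurement and coding are not blind, or that nobody in the trial is blind. The article does not support this. It does not say who measures or who codes, and a journal article may leave staffing to the full protocol. That objection stands and limits the conclusion.

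Several further points narrow the concern:

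- Goals are set in all three arms, so they can be coded blind if separated from plans and imagery. Nothing says that they are coded together.
- If-then plans and imagery steps are intervention checks with no control counterpart, so coding them cannot distort a comparison with control.
- Nobody is named as doing the matching of ID to phone number, and the sample message is generic. That the researcher can identify every text-arm participant is a plausible inference, not a stated fact.
- Compliance assessment is given to the research team, which does not by itself show that the researcher is unblinded.
- Self-completed outcomes depend mainly on what participants know. Text-arm participants know that they receive messages, but the article does not say whether they know what the other arms receive. Reassigning staff tasks would not change this.

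One could also argue that the blinded researcher and the texting researcher are different people. The article does not say so, and uses the same term for both. None of these points removes the contradiction between the blinding sentence and the tasks given to the researcher.

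**Conclusion.** The blinding statement is wrong as written. Researcher blinding is contradicted by the texting task and by the evaluation of if-then plans. Because no blinded assessor or coder is named, blind outcome measurement and blind goal coding are not assured. It is not shown that they are absent.

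The texting concerns about 34 of 102 participants and the plans about 68, assuming equal arms and full recruitment. The direction and size of any bias cannot be derived from the article. The primary outcome, scale weight, is among the less exposed measures. Tape-measured waist and hip and the coded goals are the most exposed. The point should be put right, but it does not by itself undermine the primary comparison.

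**What to change.** 1. Have the research assistant who already handles allocation hold the ID-to-phone list, send the texts and the personalised handouts, and handle the plan and imagery responses, including the compliance check.
2. Keep that assistant out of outcome measurement.
3. Keep those who take clinic measurements, and those who code goals, from arm information. Because session length can reveal the arm, staff who run the baseline video session should not take the 6- and 12-week measurements. Code goals with the plan and imagery fields removed.
4. Delete the double-blind label and state who is blind to what. Call the trial outcome-assessor blind only if measurers are in fact kept from arm information. Say that participants are not told the hypotheses only if that is true.

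The cost is some reassignment of tasks, with compliance checked by the assistant rather than the researcher. The description of the assistant as naïve to the study's purpose may need revising once that person handles plans and texts. The article gives no staff numbers, so it is an assumption that existing staff can cover these roles. If the tasks cannot be separated, correcting the blinding statement alone costs nothing and is the minimum.
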